#### Secondary Outcomes

The variables expressing the psychological well-being outcomes will be assessed by administering self-report questionnaires at the beginning (screening and week 0) and at the end (week 6) of the intervention (Textbox 2 provides a detailed overview of the questionnaire adopted). The end points to be measured include the scores of individual questionnaire items, the average scores of the questionnaires, and the differences between the average scores of the questionnaires at 2 survey times. In addition, the Perceived Stress Scale (PSS) [38] will be administered during a follow-up conducted 4 months after the study’s conclusion.

Both the clinical and usability tests will yield within-subject and between-subject comparison results.

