##### UX and Usability Evaluation

The ITA BUS B [36] is a tool designed to evaluate the ease of use, effectiveness, and user satisfaction in interacting with the chatbot. While it is commonly used with artificial intelligence (AI)–powered chatbots, it is also applicable to other types of chatbot systems [36,40,41]. The 11 items are rated on a 5-point Likert scale, where 1 means “strongly disagree” and 5 means “strongly agree,” resulting in a total score ranging from 11 to 55. The areas investigated are as follows: perceived accessibility to chatbot functions, perceived quality of chatbot, perceived quality of conversation and information provided, perceived privacy and security, and time response.

SUS [35] is a quick and reliable tool for evaluating the usability of systems. Consisting of 10 items with Likert-type answers from 1 (“strongly agree”) to 5 (“strongly disagree”), the questionnaire provides a global score that reflects the ease of use and applicability of a system or product. The SUS yields a single number representing a composite measure of the overall usability of the system being studied, with a global score that can range from 0 to 100, depending on the degree of agreement with sentences such as “I found the system very cumbersome to use.”

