UES-SF [34] measures user engagement with digital technology. Consisting of 12 items, the scale offers a quick but practical assessment of user engagement. Each item is rated on a 5-point Likert scale ranging from 1 (“strongly disagree”) to 5 (“strongly agree”), yielding a total score between 12 and 60. The questionnaire consists of four factors: (1) focused attention, which indicates the feeling of being immersed in the interaction; (2) perceived usability, which is the negative effect experienced due to the interaction and the effort expended; (3) aesthetic attractiveness, which represents the graphical and visual appeal of a digital solution; and (4) the reinforcement factor (reward). The latter is a single factor that includes duration, which evaluates the overall success of the interaction; novelty, which examines the general interest related to the interaction with a digital solution; and the perceived engagement factor, which evaluates the overall enjoyment of the interaction. As the questionnaire was not available in Italian, it was translated using the back-translation procedure. The 4 scales show good internal reliability, as follows: focused attention (ω=0.82), perceived usability (ω=0.86), aesthetic attraction (ω=0.84), and reinforcement (ω=0.81).

uMARS [37] is a tool for evaluating the quality of mobile apps. It provides a 20-item measure that includes 4 objective quality subscales—engagement, functionality, esthetics, and information quality—and 1 subjective quality subscale. One further subscale, consisting of 6 items, is added to measure users’ perceived impact of the evaluated app. This allows participants to obtain an in-depth and multidimensional evaluation of the quality of mobile apps. Each item offers answers on a Likert scale from 1 to 5, with 1 corresponding to “insufficient” and 5 to “excellent.”

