##### Psychological Assessment

The Coping Orientation to Problems Experienced‐New Italian Version 25 (COPE-NVI-25) [42] is a shortened version of the Coping Orientation to Problems Experienced Inventory, designed to evaluate different coping strategies individuals use to deal with stress. This 25-item questionnaire explores strategies such as active coping, planning, and acceptance, providing a complex picture of an individual’s coping behavior. Specifically, 5 dimensions are examined: problem orientation, transcendent orientation, positive attitudes, social support, and avoidance strategies. These dimensions are assessed using a Likert scale ranging from 1 (“I never do it”) to 4 (“I often do it”), resulting in a total score between 25 and 100.

The Emotion Regulation Questionnaire [43] is a tool that evaluates 2 main emotion regulation strategies: expressive suppression and cognitive reappraisal. The questionnaire includes 10 items, with responses on a Likert scale from 1 (“strongly disagree”) to 7 (“strongly agree”), and is used to understand how individuals control and modify their emotional reactions in various contexts. On the basis of the answers, the score can vary from 10 to 70. Balzarotti et al [44] translated and validated the questionnaire in Italian, showing good psychometric characteristics.

GHQ-12 [39] is a self-assessment tool designed to identify mental health disorders and to monitor general psychological well-being. Because of its brevity, GHQ-12 has become one of the most widely used tools for detecting psychological distress. GHQ is widely used in clinical, research, and public health settings. The 12 items of the questionnaire are formulated to investigate how the individual has felt recently concerning psychological symptoms (such as anxiety and depression), ability to cope with daily situations, sleep disorders, and somatic symptoms. The response is based on a 4-point Likert scale, ranging from “not at all” to “much more than usual,” with a maximum score of 36.

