The General Self-Efficacy Scale (GSE) [45] is a psychometric tool designed to evaluate an individual’s general perception of self-efficacy, that is, confidence in organizing and executing the actions necessary to manage potentially stressful or difficult situations. The GSE consists of 10 statements on which respondents must express their level of agreement on a Likert scale ranging from 1 (“not at all true”) to 4 (“exactly true”). The scale items explore various aspects of self-efficacy, such as the ability to solve problems, overcome obstacles, and handle unexpected situations. The total score, obtained by adding the scores of all the items, reflects the general level of self-efficacy perceived by the individual and can vary from 10 to 40, with a higher score indicating more self-efficacy.

K-10 [28] is a widely used screening tool to measure psychological distress. The K-10 is a short questionnaire composed of 10 items that investigate the frequency of psychological symptoms experienced by the individual in the last month, such as nervousness, sadness, tiredness, and feelings of hopelessness, for example, “During the last 30 days, about how often did you feel tired out for no good reason?” Each question is rated on a 5-point scale, ranging from “none of the time” to “all of the time.” Total scores range from 10 to 50, with higher scores indicating greater psychological distress (scores ≥30 suggest a high likelihood of a severe mental disorder).

The Multidimensional Psychological Flexibility Inventory (MPFI) [46] is a tool designed to assess psychological flexibility across multiple dimensions. It investigates how people adapt their thoughts and behaviors in response to changing situations and challenges. The MPFI focuses on various aspects of psychological flexibility. In particular, there are 6 scales for flexibility (acceptance, present moment awareness, self as context, defusion, values, and committed action) and 6 scales for inflexibility (experiential avoidance, lack of contact with the present moment, self as content, fusion, lack of contact with values, and inaction), according to the Hexaflex model [46]. For each of these dimensions, there are 5 items with responses ranging from 1 (“never true”) to 6 (“always true”).

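### Pre-post change is defined on whole-questionnaire averages, which dilute or mask opposing changes on the ERQ and MPFI and, to a lesser degree, the COPE-NVI-25

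*Protocol article*

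**What the plan says.** Under Secondary Outcomes the protocol's end points include individual item scores, "the average scores of the questionnaires, and the differences between the average scores of the questionnaires at 2 survey times". The end-point text under Primary Outcomes is worded in almost the same way. Neither section names a subscale or composite score, and change is defined only on the questionnaire averages.

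Psychological Assessment then describes the instruments:

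- **ERQ.** It "evaluates 2 main emotion regulation strategies: expressive suppression and cognitive reappraisal" with 10 items scored 1 to 7. One range follows: "On the basis of the answers, the score can vary from 10 to 70".
- **COPE-NVI-25.** It has 25 items scored 1 to 4 over five dimensions, among them problem orientation and avoidance, "resulting in a total score between 25 and 100".
- **MPFI.** It has "6 scales for flexibility" and six for inflexibility, each with 5 items scored 1 to 6. No total is printed.

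The ranges 10 to 70 and 25 to 100 are the plain sums of all items (10×1 to 10×7; 25×1 to 25×4). No reversal is stated for any of the three.

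The Results section plans to use the MPFI, COPE-NVI-25 and ERQ as predictors, again without subscales. It also lists significant change in the psychological variables among the benchmarks for moving to a larger trial.

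**The concern.** Each of these instruments holds scales that a stress-management programme based on acceptance and commitment therapy could be expected to move in opposite directions: flexibility up and inflexibility down, reappraisal up and suppression down, problem orientation up and avoidance down. If all items are averaged as they stand, a gain on one side is offset by a gain on the other. The pre-post difference then understates the change or misses it.

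The same pooled score would be hard to interpret as a predictor, because one value can arise from quite different profiles. Since change in the psychological variables is a progression benchmark, a masked change could count against a larger trial for a reason that lies in the scoring.

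**Working it through.** **1. The plan's own figure.** Sample Size gives α = .025, power 0.80, mean difference 1.00 and SD 2.00, so d = 1.00/2.00 = 0.50 and n = 41. For a paired t test with two-sided α = .025, the noncentrality is 0.50×√41 = 3.20 and the noncentral-t power is 0.805. The smallest n that reaches 0.80 is 41, so the figure reproduces. With 40 completers (50×0.8) power is 0.793. This is the yardstick for one subscale that changes by 0.5 SD.

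**2. Model for a pooled average.** Let w be the share of items on the side where improvement means a fall, with no reversal. Let both sides improve by 0.5 SD of change, let the item-mean changes have equal SD, and let ρ be the correlation between the two changes. Then

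d(pooled) = [(1−w)×0.5 − w×0.5] / √[(1−w)² + w² + 2w(1−w)ρ].

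The document supplies w only for the MPFI (6×5 = 30 of 60 items). The other splits, ρ from −0.5 to 0.3, the equal SDs and the 0.5 SD gain on both sides are assumptions.

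**3. Results at n = 41, two-sided α = .025**

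| Score | w | d at ρ = −0.5 | d at ρ = 0.3 | Power |
|---|---|---|---|---|
| Any one subscale | – | 0.50 | 0.50 | 0.80 |
| MPFI pooled | 0.5 (document) | 0 | 0 | 0.025 |
| ERQ pooled | 0.4 (assumed: 4 of 10 suppression items) | 0.1/√0.28 = 0.19 | 0.1/√0.664 = 0.12 | 0.14 to 0.07 |
| COPE-NVI-25 pooled | 0.2 (assumed: avoidance 5 of 25 items) | 0.3/√0.52 = 0.42 | 0.3/√0.776 = 0.34 | 0.63 to 0.45 |

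For the COPE-NVI-25 the 20 other items are treated as one block that improves by 0.5 SD. A power of 0.025 for the MPFI is simply α.

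**4. A second set of ERQ assumptions.** Take sum-score change SDs of 5 (reappraisal) and 4 (suppression). The total changes by 0.5×5 − 0.5×4 = 0.5. Its SD is √(25 + 16 + 2r×20), which is √33 = 5.7 at r = −0.2 and √53 = 7.3 at r = 0.3. So d = 0.09 to 0.07, and power at n = 40 is 0.047 to 0.038. Across both sets the ERQ total has d of about 0.07 to 0.19. An even 5/5 split with equal SDs would give 0.

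The values of d do not depend on the significance level. The power figures use .025 from Sample Size; Quantitative Analysis names .05.

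**The case against.** **The end-point list is open and includes item scores.** This stands: the averages are not the only measure, and the data needed for subscales are kept. But item scores are not subscale scores, and the only change end point is the difference between averages.

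**The wording on averages is ambiguous.** It could mean sample means of whatever score each instrument yields. The descriptions also lean towards dimension scoring: the MPFI is presented only as twelve scales, and the COPE-NVI-25 text speaks of examining five dimensions. For the MPFI this carries weight, because pooling follows only from the general wording. For the ERQ and COPE-NVI-25 it carries less, because a single sum is printed for each.

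**A full protocol or analysis plan could settle the scoring.** That is true of scoring keys in general. Here, however, the article prints totals over opposing constructs and ties change to averages, which is more than an omitted detail.

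**Masking needs both sides to move.** The document gives no expected direction for suppression or for any COPE dimension; it anticipates only better flexibility and emotion regulation. The figures above are therefore conditional. A reader might infer that all three instruments would show no change. The COPE-NVI-25 figures do not support that, and for the ERQ the size depends on inputs the document does not give.

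**The primary outcomes.** A reader might also infer that a usability score is mis-signed. In UX and Usability Evaluation the UES-SF total includes "perceived usability, which is the negative effect experienced due to the interaction and the effort expended" with no reversal stated, and the SUS is printed with 1 as strong agreement, opposite to the UES-SF and ITA BUS B. An article commonly leaves out item reversal. The SUS anchors may be a slip of description, and instruments may differ in their anchors. Neither shows a scoring error; both are wording to confirm.

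**These are secondary outcomes in a single-arm proof-of-concept study.** The protocol describes the questionnaires as collecting descriptive data, and the sample size does not rest on these totals. This limits the severity.

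**Conclusion.** The point holds, with moderate severity, for change end points on the ERQ and COPE-NVI-25, where single totals without reversal are printed. It holds for the MPFI to the extent that the general wording on averages is applied to it.

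If both sides improve by 0.5 SD of change, a whole-questionnaire score loses the effect for the MPFI, most of it for the ERQ and part of it for the COPE-NVI-25. The result for the MPFI is exact only with equal change SDs on the two sides; the ERQ and COPE-NVI-25 sizes rest on the assumptions in the working.

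The practical risk is to the psychological-change benchmark, which is one of several alongside engagement, retention, usability and app function. No error in a primary outcome is shown.

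**What to change.** In Secondary Outcomes, replace the questionnaire average for these three instruments by named scores:

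- ERQ: cognitive reappraisal and expressive suppression, separately.
- COPE-NVI-25: the five dimensions, separately.
- MPFI: a flexibility composite and an inflexibility composite, separately.

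State the expected direction of change for each, and drop the ERQ and COPE-NVI-25 totals as end points. Use the same named scores where the Results section brings these instruments in as predictors, and say which of them count towards the psychological benchmark.

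The items are already in the data collection, so the cost is wording plus a few more secondary scores. Report these descriptively with confidence intervals, so that the added scores do not become added significance tests. While editing, confirm the UES-SF item keying and the SUS response anchors.

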### Data Collection

The data collection process will take place in all the phases of the research, starting with recruitment and ending with follow-up.

#### Phase 0: Recruitment

Sociodemographic data collection will be carried out by the health professionals at the Breast Unit (physicians and case manager nurses) using a prestructured form. After informed consent is obtained, each form will be assigned a unique alphanumeric code. The parameters requested from participants will be (1) date of birth, (2) oncological disease history (ie, date of first cancer diagnosis, date of tumor removal surgery, date of any other interventions carried out or planned, and date of last neoadjuvant or adjuvant chemotherapy or radiotherapy treatment or if still ongoing), (3) maximum education grade, (4) employment, (5) marital status, and (6) current or previous experience of psychological support (exclusion criterion 7 verification).

#### Phase 1: Screening

To fulfill the verification of the inclusion criteria from 7 to 9 and the exclusion criteria 5 and 6, the researchers will administer the screening questionnaires through LimeSurvey (LimeSurvey GmbH; Textbox 2).

After processing the results of the screening questionnaires and the various sociodemographic inclusion criteria, the women will be contacted again, and the following scenarios will open.

First, the participant does not meet the inclusion criteria due to demonstrating a markedly positive state of psychological well-being, as indicated by a stress level <15.9 on the Kessler Psychological Distress Scale (K-10) [28], a general well-being score <3 on the General Health Questionnaire (GHQ) [39], and a general well-being score >80 on the “Mental Health” scale of the Short Form Health Survey 36 (SF-36) [29]. In such cases, the women will not be enrolled in the study, and the reasons for exclusion will be shared along with the screening questionnaire results, but upon the participant’s request.

Second, the participant does not meet the inclusion criteria due to exhibiting a markedly negative state of psychological well-being or signs of psychopathology, as indicated by a score <30 on mental health scale of the SF-36 and a K-10 score >29.9. In addition, in the second case, the participant will not be able to be enrolled in the study, and the reasons for exclusion from the study will be returned, and only upon request of the participant will the results obtained from the screening questionnaires be returned. Furthermore, indications of local services to contact for problems will be appropriately provided. This is to provide the participant with a structured and agreed system of referral to a qualified support service and taking charge where appropriate.

Third, the participant meets the inclusion criteria. In this case, the participant is enrolled in the study. The participant will also be asked if they would like to participate in a qualitative interview and in compiling a last questionnaire about stress 4 months after delivery. In case of positive feedback, the telephone number will be collected to facilitate contacts and follow-up interviews.

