**Inclusion criteria**
Have a diagnosis of stage 0, I, II, or III breast cancer (BC)Be a female patient under the care of the Breast UnitBe aged ≥18 years (Italian legal age)Have a smartphone with internet access and the ability to download the app and be able to use itBe a resident of the Autonomous Province of TrentoKnow and understand the Italian languageHave a moderate level of psychological distress, defined by a score between 15.9 and 29.9 on the Kessler Psychological Distress Scale, with higher scores indicating more severe distress [28]. This range aligns with the inclusion thresholds used in World Health Organization (WHO) studies using the RESPOND protocol [17].Have a general well-being score of ≥3 on the General Health Questionnaire, consistent with the inclusion criterion used in World Health Organization studies using the Self Health Plus protocol [14].Obtain a score between 30 and 80 (cutoffs identified based on the literature on the Short Form Health Survey 36 [SF-36] instrument in patients diagnosed with BC [29,30]) on the “Mental health” scale of the SF-36 questionnaire.

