**Exclusion criteria**
Patients unable to provide informed consent (prerequisite for participation in the study)Inadequate understanding of the Italian languagePatients aged >75 yearsWomen with metastatic BC (stage IV), those in the metastatic phase, receiving palliative care, or with a life expectancy of <1 yearObtain a score <30 on the “Bodily Pain” scale of the SF-36, indicating severe pain levels [29,30]Suicidal tendencies, depression, or other psychiatric diagnosesAlready receiving psychological or psychotherapeutic care at the time of recruitment

Health professionals at the Breast Unit will verify the inclusion and exclusion criteria related to the sociodemographic data (phase 0), while psychologists will assess the psychological screening data (phase 1).

Participants will be required to sign an informed consent form during recruitment (phase 0), following a comprehensive explanation of the project, its objectives, data collection, management, processing procedures, the required level of involvement, the study duration, and confidentiality matters. They will be informed that they can withdraw from the study at any time without providing a reason and that doing so will not affect the quality of their care or interfere with their treatment. Informed consent must be given freely and in writing, accompanied by a data processing authorization form, before joining the study. Participants must provide written informed consent. They will also receive a privacy policy statement explaining how their personal data will be processed during the study and must provide explicit consent for its use. Copies of the informed consent and privacy forms will be provided to participants and available in a dedicated section of the app.

To promote participant engagement and retention throughout the 6-week intervention, specific features were designed to sustain interest and minimize dropout, such as incorporating gamification elements, providing regular feedback or progress tracking, scheduling personalized reminders, and offering small recognition for continued participation. No monetary compensation was provided.

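### The screening text ties local-service information to two severe scores together, although one severe score is enough to make a woman ineligible

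*Protocol article*

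**What the plan says.** The inclusion criteria (Textbox 1) list the screening limits as separate conditions. K-10 must show moderate distress, "defined by a score between 15.9 and 29.9 on the Kessler Psychological Distress Scale". GHQ must be at least 3. For the SF-36 mental health scale the requirement is "Obtain a score between 30 and 80".

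Under Data Collection, the section Phase 1: Screening says that once the screening results are processed "the women will be contacted again, and the following scenarios will open". It gives three:

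- **Scenario 1:** the woman is ineligible "due to demonstrating a markedly positive state of psychological well-being", shown by K-10 <15.9, GHQ <3 and mental health >80.
- **Scenario 2:** she is ineligible because her well-being is markedly poor or there are signs of psychopathology, "as indicated by a score <30 on mental health scale of the SF-36 and a K-10 score >29.9". Only here does the text add that "indications of local services to contact for problems will be appropriately provided".
- **Scenario 3:** she meets the inclusion criteria and is enrolled.

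The Psychological Assessment section gives K-10 a range of 10 to 50 and reads a score of 30 or more, taken alone, as pointing to a probable severe mental disorder.

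**The concern.** The eligibility rule and the signposting rule use the same cutoffs but join them differently. Either severe score makes a woman ineligible, whereas the service information is attached to both severe scores together. A woman whom the study has measured as too distressed on one scale is turned away, and the text does not say that she is told where to find help.

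The authors describe this step as an organised route to qualified support. Women already in psychological or psychotherapeutic care are excluded, so those screened are largely without such care. The stake is participant safety at screening. The pilot's estimates do not depend on it.

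**Working it through.** The plan gives no figure to reproduce. The check is a count of which score patterns each scenario covers.

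**Inputs.** K-10 has three bands (<15.9, 15.9–29.9, >29.9), GHQ has two (<3, ≥3) and SF-36 mental health has three (<30, 30–80, >80). The cutoffs come from the inclusion criteria and Phase 1: Screening. Total patterns: 3 × 2 × 3 = 18.

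**Scenario reached, with each *and* read literally.**

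| | Mental health <30 | Mental health 30–80 | Mental health >80 |
|---|---|---|---|
| K-10 <15.9 | none | none | 1 if GHQ <3, otherwise none |
| K-10 15.9–29.9 | none | 3 if GHQ ≥3, otherwise none | none |
| K-10 >29.9 | 2 | none | none |

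1. Patterns assigned: scenario 1 has 1, scenario 2 has 2 (either GHQ level) and scenario 3 has 1. That is 1 + 2 + 1 = 4, leaving 18 − 4 = 14 unassigned.
2. Patterns with at least one severe score: 6 with K-10 >29.9, plus 6 with mental health <30, minus 2 with both, which is 10.
3. Patterns with exactly one severe score: 10 − 2 = 8. All 8 are ineligible and all 8 are among the 14 unassigned.
4. Of these 8, 4 pair opposite extremes (K-10 >29.9 with mental health >80, or K-10 <15.9 with mental health <30) and are unlikely in practice. The other 4 are plausible: K-10 >29.9 with mental health 30–80, and K-10 15.9–29.9 with mental health <30, each at either GHQ level.

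**Examples.** K-10 35 with mental health 44, and K-10 25 with mental health 20, are both ineligible and both outside every scenario. So is the maximum K-10 of 50 with mental health 44.

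**With *or* in scenario 2 only.** Scenario 2 covers all 10 patterns with a severe score. It cannot overlap scenario 1, which needs K-10 <15.9 and mental health >80, nor scenario 3, which needs both scores in range. The patterns still unassigned number 18 − 10 − 1 − 1 = 6, and none of them contains a severe score.

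These are counts of logical patterns, not of women.

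**The case against.** The strongest reply is that the conjunction was never meant as a joint test. Scenario 2 describes a state of poor well-being or signs of psychopathology and then names what indicates it. One severe score already fails the inclusion criteria, and the K-10 description treats a high score alone as serious. A short summary of too well, too distressed and eligible is a plausible intent. On that reading every severe score reaches scenario 2 and nobody loses signposting. This stands as an account of what the authors may have meant. It does not remove the mismatch in a rule that is written out with cutoffs.

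Judgement is also built into the step. Psychologists carry out the screening, the women are contacted again, and the service information is to be given as appropriate. This stands too, and it lowers the weight of the point.

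A reader might be tempted by three stronger conclusions that the document does not support:

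- **That severely distressed women will be sent away without help.** Nothing in the text directs that; the article only fails to state the step for them.
- **That no reading of the scenarios works.** If every *and* is read as *or*, 7 of the 18 patterns match both scenario 1 and scenario 2. But scenario 1 does not forbid signposting, and if only scenario 2 lists alternatives there is no overlap.
- **That women excluded for bodily pain, or for suicidal tendencies or a psychiatric diagnosis, have been overlooked.** The same screen verifies "the inclusion criteria from 7 to 9 and the exclusion criteria 5 and 6", but scenarios 1 and 2 are framed around failing the inclusion criteria on well-being. How the other exclusions are handled is detail that a condensed article may leave to the full protocol.

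**Conclusion.** The point holds as a mismatch between two stated rules. Read literally, all 8 patterns with exactly one severe score are ineligible, unassigned and without a stated signposting step; 4 of the 8 are clinically plausible.

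This rests on taking the conjunction in scenario 2 at face value and on the article's own cutoffs. It needs no distributional assumption. The document gives no distribution of screening scores, so the number of women affected cannot be estimated.

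It is a minor participant-safety correction, worth making because the K-10 description itself treats one high score as serious. Eligibility, sample size and analysis are not affected.

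**What to change.** In Phase 1: Screening, define scenario 2 as SF-36 mental health <30 **or** K-10 >29.9, whatever the GHQ score. Keep scenario 1 for women with no severe score. State that every woman in scenario 2 is given the local-service information.

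The change is essentially one conjunction. Screened women are already contacted again, so the only added work is service information for somewhat more of them, including some who may not need it.
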